**STATISTICIAN:** **ASSOCIATE PROF [name]**

**DEPARTMENT OF COMMUNITY HEALTH UKMMC**

**CHAPTER 1**

**Introduction and Literature Review**

**1.1 Parkinson’s Disease**

Parkinson’s disease (PD) is a chronic progressive neurodegenerative disease caused by the depletion of dopaminergic neurons in the substantia nigra. It is characterised by resting tremor, rigidity, bradykinesia and postural instability. Apart from these motor symptoms, non-motor symptoms (NMS) of PD are becoming increasingly recognised (Table 1.1). The diagnosis of PD is a clinical one based on the UK Parkinson’s Disease Society Brain Bank Clinical Diagnostic Criteria (Appendix I). No diagnostic test exists. However, PD needs to be differentiated from other causes of parkinsonism such as secondary Parkinson or Parkinson Plus (table 1.2).

Epidemiology

Parkinson’s disease is the second most common neurodegenerative disorder after Alzheimer’s disease. The worldwide incidence of PD is 1 in 1000 with a mean age of onset of 55-60 years. The disease is uncommon before the age of 40; and the prevalence increases by about 1% after the age of 60 years1 and to 3% in people at the age of 80 and older.

Due to a dearth in studies, the prevalence of PD in Malaysia is largely unknown. However, a study of PD prevalence in Singapore2 in 1994 showed the crude prevalence of 0.29% in individuals aged 50 and above. Analysis of prevalence in different age groups showed an increase in prevalence in higher age groups up to 25-fold for 80 and above. Inter-racial prevalence rates analysis in the study also showed no difference among Malays (0.23%), Chinese (0.27%) and Indians (0.27%).

Pathogenesis and Causes

The hallmark of idiopathic PD is degeneration of the dopaminergic neurons pathway at the substantia nigra pars compacta of the midbrain3 with widespread presence of cytoplasmic inclusions known as Lewy bodies throughout the central and autonomic nervous system. Lewy bodies are abnormal intracytoplasmic aggregates of α-synuclein present in highly selected neurons. In Braak stages of PD4, he observed that deposition of the proteinaceous material started at dorsal motor nucleus and advanced upwards thereon. The process continue to progress and once the motor symptoms developed, patients are already at the later staged of the disease. Braak described 6 stages of PD progression, and the deposition of intracytoplasmic Lewy bodies at substantia nigra occurred at Stage III.

Pesticides and herbicides

Exposure to pesticides or herbicides have long been suggested as a risk factor for PD. 1-methyl-4-phenyl-1,2,3,6-tetrahydropyridine (MPTP), a byproduct of illicit heroin synthesis, is known to induce parkinsonism. Investigators have also made the observation that the herbicide paraquat (N,N′-dimethyl-4,4′-bipyridinium dichloride bore a resemblance to 1-methyl-4–phenylpyridinium (MPP), an active metabolite of MPTP. Rajput *et al5* , in a study of PD patients in Canada, found that exposure to pesticides positively correlated with increased incidence of PD-like symptoms. Liou *et al6* showed that intracerebral injection of paraquat resulted in loss of dopaminergic neurons and depletion of dopamine in the substantia nigra. A Swedish study found that handling pesticides was associated with increased risk of PD by threefold7. Another study in Brazil also showed that chemical exposure increased the risk of PD8.

Cigarette smoking, caffeine consumption and alcohol

1. Cigarette smoking and caffeine have been shown to have a protective effect against PD. The largest comprehensive study was conducted in 1992 where a group of 14 436 twins from the National Academy of Sciences-National Research Council World War II Veteran Twins Registry were interviewed. They showed that the risk of PD was inversely associated with number of pack years smoked9. Interestingly, cigarette smoking does not show a disease-modifying effect when patients who have already been diagnosed with Parkinson’s started smoking10.The negative association between PD and coffee/caffeine intake has been demonstrated consistently. As a part of Honolulu Heart Program11, data analysed among 8004 Japanese-American men demonstrated that higher caffeine intake is associated with a significantly lower incidence of PD. Both nicotine and caffeine have been demonstrated to prevent neurostriatal degeneration in mice and primates that have been treated with MPTP/MPP. Caffeine was shown to prevent the development of akinesia when given to these dopamine-depleted mice12.There is no significant association between alcohol consumption and PD13.

The difference in gender prevalence, where male is more preponderance to develop PD, support the possibility of genetic contributions to IPD. Although the genes responsible for Parkinson’s disease have been found, they are not found in most of PD patients.

Treatment and clinical progression

There is no treatment to reverse the neurological disability in PD. Current treatment are only for symptomatic relief by replenishing dopamine to improve motor function and quality of life. Levodopa is the mainstay of treatment for PD, and it dramatically improves parkinsonian symptoms in the early to moderate stages of the disease. However long term use will cause wearing off symptoms and peak dose dyskinesia14. Hence, clinicians choose dopamine agonist such as selegiline or pramipexole, instead to delay the use of levodopa especially in younger patients. Other medications that are used with PD are decarboxylase inhibitor such as carbidopa or benserazide to reduce peripheral degradation of levodopa and monoamine oxygenase inhibitor (MAOI) such as selegiline.

**TABLE 1.1 Non-motor Manifestations of Parkinson’s Disease**

(from Simuni & Sethi, Nonmotor Manifestations of Parkinson’s Disease Ann Neurol 2008;64 (suppl):S65-S80)

Neuropsychiatric symptoms

Depression, apathy, anhedonia, anxiety

Dementia

Impulse control disorders

Hallucinations, delusions (usually medications induced)

Sleep Dysfunction

Disorders of sleep initiation and maintenance

Insomnia, poor sleep efficiency

Primary sleep disorders

Restless legs syndrome,

Periodic legs movement disorder

Sleep apnea (obstructive and central)

Parasomnias

REM sleep disorder

Non-REM sleep-related movement disorders

Vivid dreaming

Excessive Daytime Sleepiness

Autonomic Dysfunction

Bladder dysfunction

Orthostatic hypotension

Hyperhidrosis

Sexual dysfunction

Gastrointestinal Symptoms

Constipation

Hypersalivation

Dysphagia

Sensory symptoms

Pain

Olfactory dysfunction

Visual symptoms (diplopia, vision blurring)

Other symptoms

Fatigue

Weight loss

Weight gain (can be medication induced)

**TABLE 1.2 Parkinson-plus syndrome and Secondary Parkinsonism**

| **Parkinson-plus syndrome** | **Secondary Parkinsonism** |
| --- | --- |
| Multiple-system atrophy  (Olivopontocerebellar atrophy  Shy-Drager syndrome)  Progressive supranuclear palsy  Cortico-basal ganglionic degeneration  Vascular Parkinsonism  Dementia with Lewy Bodies | Wilson’s Disease  Drug induced Parkinsonism   - dopamine antagonist (neuroleptic agents, antiemetics)haloperidol - calcium channel antagonists (flunarizine, cinnarizine) - amiodarone - sodium valproate - lithium   Toxic induced – manganese, carbon monoxide, MPTP  Postencephalitic (eg. Encephalitis lethargica, AIDS encephalitis)  Traumatic  Neoplastic  Genetic (DYT12, Parkin mutation, DYT3, ARJP) |

**1.2 *Helicobacter pylori***

*Helicobacter pylori* is a spiral-shaped, gram-negative bacillus that inhabits the gastric mucosa. It is one of the most common infections found in humans worldwide. It was first discovered by Warren and Marshall in 1982 and was then called *Campylobacter pylori*. By the end of the 1980s there was a recognised association between *H. pylori* and antral gastritis and by early-to-mid 1990s further research showed evidence of a link between chronic *H. pylori* infection and gastric malignancies.

The prevalence of *H. pylori* infection varies worldwide ranging between 20-80%15. This variation of prevalence is due to several factors such as age, socioeconomic status and ethnicity. In their review, Pounder and Ng16 identified two major patterns of *H. pylori* infection prevalence. The first group showed a high prevalence of *H. pylori* infection before the age of 10 which remained high across all age groups (Appendix II). The second group had a low childhood prevalence which increased with age which occurred in developed countries.

In Malaysia, an overall prevalence of 26-60% was noted. Goh et al17 studied the prevalence of *H. pylori* infection in patients undergoing endoscopy in the University Hospital in Kuala Lumpur between 1994-1995. They found that the Indian race had the highest prevalence of *H. pylori* than either Chinese or Malays with seropositivity of 61.8%, 48.5% and 16.4% respectively. A study done by Gurjeet et al18 among endoscoped patients in north eastern Peninsular Malaysia in 2003 found a low prevalence of 13.5%. They also found similar differences in racial distribution of prevalence for Malays (6.6%), Chinese (24.1%) and Indians (28.6%). Another study by Uyub19 looking at 5,370 healthy blood donors in Northern Peninsula showed a lower prevalence of 14.2%.

Humans are the only known host of *H. pylori*. Its mode of transmission is still not fully understood. However, a hypothesis of transmission via feco-oral contamination has been made based on several studies. *H. pylori* has been cultured from vomitus, diarrhoeal stools, saliva supporting this theory. A study of household members who were exposed to another household member infected with *H. pylori* showed an increase of 4.8 fold risk of infection, further supporting human-to-human transmission via faeco-oral mode. A possibility of contracting via contaminated drinking water is still unproven although the presence of *H. pylori* DNA PCR has been documented in drinking water in Peru20 that correlates with a high *H. pylori* infection rate among children from low-income group21.

Some identified risk factors for high prevalence in a given subpopulation are overcrowding, type of drinking water, lack of toilet facilities during childhood, lower family income and lower educational level22.Cigarette smoking, alcohol and coffee consumption are lifestyle factors that have been studied extensively in relation to *H. pylori* infection. In one cross sectional study, Brenner *et al*23 found alcohol consumption to have a protective effect against *H. pylori* infection while coffee drinking has the opposite effect.

*H. pylori* is highly adaptive to survive the acidic gastric environment. It produces a urease enzyme which converts urea into carbon dioxide and ammonia. Their flagelli improves their motility to move deeper across the gastric mucous layer. *H. pylori* have a high affinity for mucosal epithelial cells because of a specific bacterial component found on the surface of the bacteria. Once bound to the gastric mucosa epithelia, they continuously trigger gastric inflammation. Recent studies have suggested that *H. pylori* may invade the cytoplasm of the gastric epithelial cells and are thus able to survive for prolonged periods. This might explain their ability to induce a strong immune response and cause gastric disease. *H. pylori* also induce systemic and mucosal humoral responses. Once contracted, *H. pylori* infection does not resolve spontaneously. Instead, it remains within the stomach wall, continuously stimulating host inflammatory reactions.

*H. pylori* infection has been incriminated as the cause of many conditions such as peptic ulcer disease24, atrophic gastritis25, gastric MALToma26, 27 and gastric adenocarcinoma28, 29. There were also several extragastric diseases that were associated with *H.pylori* infection such as hepatocellular carcinoma, cholelithiasis, inflammatory bowel disease, idiopathic thrombocytopeania, chronic urticaria and sideropaenic anemia. Some of these conditions have evidence to show that by eradicating *H. pylori* infection, the associated condition will improve or reduce in risk. For example, in chronic urticaria30, eradication of *H. pylori* infection helped to resolve the urticaria. In peptic ulcer, eradication helped reduce the recurrence rate of the ulcer.

Association between *H. pylori* infection and gastric cancer has been well demonstrated. *H. pylori* is already considered as a type I (definite) carcinogen due to the evidence acummulated31, 32. The EUROGAST study demonstrated an increased gastric malignancy risk with 100% seroprevalence of *H. pylori* compared with seronegative populations. Seropositivity for *H. pylori* infection was associated with a threefold risk of developing gastric adenocarcinoma28.

Diagnosis of *H. pylori*

There are several methods of confirming *H. pylori* infection. Oesophagogastroduodenoscopy (OGDS) in combination with the urease test (e.g. CLO test), is useful to confirm the presence of *H. pylori*. OGDS allows direct visualisation of the gastric mucosa and allows for histopathological examination via biopsy.

A non-invasive method which is useful for noncomplicated cases is the 13C-Urea Breath test (UBT), where samples of the patient’s breath are taken at baseline and after drinking the C-13 urea. This method has been validated repetitively33-36, and is considered the gold standard. However, it lacks the benefit of viewing of the gastric mucosa and sampling for culture and sensitivity.

Serologic testing to detect *H. pylori* IgG or IgA antibodies is an alternative noninvasive test which boasts a sensitivity of 90-100% but has variable specificity of 76-96%37, 38. Other test such as PCR, salivary and urinary assays are available but not widely used due to their lack of practicality and/or poor sensitivity.

Treatment

Treatment eradication for *H. pylori* is highly efficacious39. The current recommendation for eradication was formulated at the Maastricht III Consensus Conference in March 2005. Eradication treatment for *H. pylori* consists of a proton pump inhibitor (PPI) oral esomeprazole 40mg twice daily, oral clarithromycin 500mg bd and amoxicillin 1000mg bd (or metronidazole in penicillin allergic patients) for a recommended duration of 7 to 14 days40.

**1.3 The association between PD and *H. pylori* infection**

The earliest observation that there is an association between *H. pylori* and PD was in 1966 when Strang41 found that gastric and duodenal ulcers were more common in PD patients than their age and gender-matched controls and that these ulcers preceded the diagnosis of PD by up to 20 years. Upon the discovery of *H. pylori* and its association with peptic ulcer disease, numerous studies were conducted to look for a correlation between *H. pylori* and PD.

James Parkinson himself considered that there may be an association between PD and gastrointestinal pathology when he wrote “Although unable to trace the connection by which a disordered state of the stomach and bowels may induce a morbid action in a part of the medulla spinalis, …little hesitation needs be employed before we determine on the probability of such occurrence” (pg 64, The Shaking Palsy)42.

A direct causal relationship was hypothesised by Altschuler who proposed that *H. pylori* might play a part in the biosynthetic route for MPTP or MPTP-like substance that have a direct neurotoxic effect on the dopaminergic neurons43.

In 1999, Charlett *et al.* observed that cardinal features of PD, namely bradykinesia, rigidity and abnormal posture was significantly more prevalent in siblings of PD patients (p=0.01, p<0.001 and p=0.001, respectively) compared to controls. Positive *H. pylori* serology was found in 70% of PD patients and 63% of their siblings compared to 36-43% of controls. They concluded that familial transmission of *H. pylori* might account for the significantly higher prevalence of parkinsonism in siblings of PD patients.

Chronic inflammation leading to neurotoxicity to dopaminergic neurons

Bjarnason *et al*44 found that the presence of antibodies against *H. pylori* correlated with IPD, and eradication showed improvement in the measurement of stride length. There was also a correlation between eradication therapy and reduction in inflammatory markers such as IL-6 and TNF-alpha. They hypothesised that chronic infection leads to underlying chronic inflammatory and autoantibody /molecular mimicry mechanism that leads to destruction of the dopaminergic neurons.

Hirai45 studied lipid composition of *H. pylori* and identified three cholesterol glucosidases (CG). Of interest, the similarity of the structure of the CG sterols in *H. pylori* and sterol glucosidase in cycad, which may hypothesized a possibility that *H. pylori* with certain strain that can cause parkinsonism by way of producing similar sterol glucosidase that is neurotoxic46. Cycad is a type of seed made into flour that has been known to cause ALS-PD disease in population such as in Guam island47, 48 and Kii,Japan49. Murine experimental exposure to cycad showed progressive motor and cognitive deterioration. Pathological analysis revealed that they have loss of motor neurones and loss of striatal dopaminergic terminals.

*H. pylori* and levodopa absorption

Levodopa absorption occurs in the duodenum. In advanced PD, gastric motility is impaired and this can delay the transit of levodopa through the pylorus and subsequently, prevent or delay its clinical effect. In the duodenum, any inflammatory pathology can also impair levodopa absorption. *H.pylori* infection affects L-dopa bioavailability via disruption of duodenal mucosa, the site of its absorption and local production of reactive oxygen species, which may inactivate the drug50.

Irregularity in levodopa delivery to the brain is common in PD and can lead to erratic response to levodopa and motor fluctuations. This can be attributed to impaired gastrointestinal transit or absorption of the drug.

Pierantozzi *et al.* conducted a study in which PD patients with *H. pylori* infection were randomised into eradication therapy and control groups. Serum levodopa levels were consistently higher in the eradication therapy group compared to controls. The active group was also noted to have prolonged clinical response to levodopa, more “on time” and fewer motor fluctuations50

The authors concluded that *H. pylori* infection impairs absorption of levodopa and eradication therapy is a simple and inexpensive means to aid levodopa absorption and improve clinical response.

**CHAPTER 2**

**STUDY JUSTIFICATIONS AND OBJECTIVES**

**Study justifications**

Diagnosing *H.pylori* infection in Parkinson’s patients is important as eradicating *H. pylori* not only reduces the risk of H. *pylori* complications such as duodenal ulcer and gastric carcinoma, but it will also help to improve their motor disability. Previous studies abroad have shown that eradication of *H. pylori* increased levodopa bioavailability as *H. pylori* had been shown to affect its absorption. Conducting this study among Parkinson’s patients in PPUKM will give us data for Malaysian populations.

**Study Objectives**

Primary Objectives:

- To compare the clinical response to L-dopa before and after *H. pylori* eradication therapy in the *H. pylori* infected PD group. (L-dopa ‘onset’ time (minutes) and L-dopa ‘on-time’ duration (minutes) ).

Secondary Objectives:

- To assess clinical motor improvement before and after *H. pylori* eradication therapy in infected PD group, using the UPDRS-III and PDQ39 questionnaires.

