**CHAPTER 3**

**STUDY HYPOTHESES**

1. *H. pylori* eradication improves L-dopa ‘onset’ time and prolongs the L-dopa ‘on-time’ duration.
2. PD patients with *H. pylori* infection show clinical improvement in motor disability after eradication therapy of H. *pylori*, assessed using UPDRS-III / PDQ39 questionnaires.

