4.3 Study Flow Chart

*For subject who is on proton pump inhibitor, if there is no contraindication will be withhold for 4 weeks and given a later date for Urea Breath Test

Sample recruitment

Assessment for eligibility

(Fulfillment of Inclusion criteria)

Informed consent

Patient assessment (L-dopa ‘onset’ time and ‘on-time’ duration, UPDRS-III & PDQ39) and data collection

Positive urea breath test (UBT)

Eradication therapy of H.pylori (oral esomeprazole 40mg od, oral clarithromycin 500mg bd and oral amoxicillin 1000mg bd x 14/7)

Assessment of clinical response to L-Dopa (L-dopa ‘onset’ time and ‘on-time’ duration) & clinical motor improvement using UPDRS-III and PDQ-39 Questionnaire

3/12 later

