4.5 Study protocol and study tools

Upon consent, patients will be enquired regarding their background and the data will be recorded (Appendix III). Information regarding sociodemographic characteristics (smoking history, alcohol consumption and coffee consumption), previous antibiotics use, concomitant medical conditions, current medications and any gastrointestinal symptoms will be recorded. Height and weight are measured and recorded into the data collection sheet. The clinical response to L-dopa will be documented (looking at L-dopa ‘onset’ time (minutes) and L-dopa ‘on-time’ duration (minutes)). The severity of their Parkinson’s disease will be assessed using PDQ-39 questionnaires and the Unified Parkinson’s Disease Rating Scale (UPDRS)-III.

PDQ-39 (Appendix IV)

PDQ-39 is the most widely used disease-specific patient completed rating scale in PD. It consists of 39 questions covering eight aspects of quality of life: mobility, activities of daily living (ADL), emotional well being, social stigma, social support, cognition, communications and bodily discomfort. PDQ-39 has been tested for reliability and validity51. The maximum total score for PDQ-39 is 156 points signifying a poorer quality of life, with subdivisions for mobility (40), ADL (24), emotional well being (24), social stigma (16), social support (12), cognitive impairment (16), communication (12) and bodily discomfort (12).

The Unified Parkinson’s Disease Rating Scale (UPDRS) (Appendix V)

The UPDRS is a rating scale used to assess the severity of PD. It is useful for clinicians as well as researchers to evaluate the progression of the disease and response to treatment. It is comprised of 4 parts. Part I – Mentation, behaviour and mood, Part II – self evaluation of ADLs, Part III – clinician scored motor evaluation and Part IV – Complications of therapy. The first 3 sections (I to III) are rated with a 5-point scale (0 signifying no disability and 4 signifying maximum disability) while the fourth section is used to evaluate patients with more advanced stage who are on treatment. The maximum score for each section is 16, 52, 108 and 23, respectively, giving a total of 199, being the higher the score the greater the disability from PD.

Urea Breath test protocol (Appendix VI)

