The IRIS Infra Red isotope Analyser quantifies the ratio of 13CO2 with our normal breath 12CO2 in order to measure the current *H. pylori* current infection. DOB value of more than 4.0 is considered *H. pylori* positive while DOB of less than 2.5 is considered negative *H. pylori*. If all the values fall in between the range 2.5 to 4.0, the patient is considered positive if they have taken antibiotics, PPI or H2 antagonist for the last 4 to 6 weeks. Otherwise, patient is considered as negative. The sensitivity and specificity of 13C-UBT is 98.3% and 98.6% repectively with a positive predicted value and negative predicted value of 13C-UBT is 98.2% and 90% respectively35.

Treatment for *H. pylori*

Patients with positive Urea Breath Test (positive for *H. pylori* infection) will be started on eradication therapy of *H. pylori* (oral esomeprazole 40mg twice bd, oral clarithromycin 500mg bd and oral amoxicillin 1000mg bd) for 14 days. This current recommendation was formulated at the Maastricht III Consensus Conference in March 2005 40.

Follow up visit

*H pylori*-infected Parkinsons disease patients will be followed up in the neurology clinic 3 months after eradication therapy of *H pylori*. The clinical response to L-dopa after eradication treatment of *H pylori* will be assessed (looking at L-dopa ‘onset’ time (minutes) and L-dopa ‘on-time’ duration (minutes)). The clinical motor improvement will also be assessed using PDQ-39 questionnaires and the Unified Parkinson’s Disease Rating Scale (UPDRS)-III. Patients will be guided by investigator to answer the all the questionnaires.

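### PDQ-39, which the protocol itself describes as a quality-of-life scale, is assigned to measure motor improvement in the secondary objective, hypothesis 2, the flow chart and the follow-up text

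*Protocol*

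**What the plan says.** Four places in the protocol give PDQ-39 a motor role.

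- **Chapter 2, Study Objectives (secondary).** The aim is "To assess clinical motor improvement before and after" "eradication therapy in infected PD group, using the UPDRS-III and PDQ39 questionnaires".
- **Chapter 3, Study Hypotheses, no. 2.** Infected patients are expected to "show clinical improvement in motor disability after eradication therapy of H". *pylori*, "assessed using UPDRS-III / PDQ39 questionnaires".
- **Section 4.3, Study Flow Chart.** The final assessment covers "clinical motor improvement using UPDRS-III and PDQ-39 Questionnaire".
- **Section 4.5, Follow up visit.** "The clinical motor improvement will also be assessed using PDQ-39 questionnaires", with UPDRS-III named after it.

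The descriptions of the instruments in section 4.5 say something different. Of PDQ-39: "It consists of 39 questions covering eight aspects of quality of life", and "The maximum total score for PDQ-39 is 156 points signifying a poorer quality of life". The eight domain maxima follow. UPDRS is described part by part, and Part III is the part in which the clinician scores motor function.

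The only objectives listed are the L-dopa response (primary) and motor improvement (secondary). Quality of life appears in neither the objectives nor the hypotheses.

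**The concern.** The objective and the hypothesis fix what the trial will claim. Here the claim is about motor function, but one of the two instruments behind it measures, by the protocol's own account, something broader. Lower scores on depression, social support or daytime sleepiness reduce the PDQ-39 total with no change in movement. Under the wording of the secondary objective and hypothesis 2, such a reduction could be written up as less motor disability, even with UPDRS-III unchanged.

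The reverse problem also arises. A real benefit on quality of life would be worth reporting, but no objective exists to report it under. PDQ-39's only stated purpose at follow-up is as evidence of motor change.

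**Working it through.** **Inputs** (Protocol section 4.5, PDQ-39 paragraph): mobility 40, activities of daily living (ADL) 24, emotional well-being 24, stigma 16, social support 12, cognition 16, communication 12, bodily discomfort 12; stated maximum 156.

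**1. Reproduce the stated total.** 40 + 24 + 24 + 16 + 12 + 16 + 12 + 12 = 156. This also equals 39 items × 4 points. The protocol's figure is reproduced, so the domain maxima can be relied on.

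**2. Share of the total in mobility and ADL.**
- Mobility + ADL = 40 + 24 = 64; 64/156 = 41.0%.
- All other domains = 156 − 64 = 92; 92/156 = 59.0%.
- Mobility alone = 40/156 = 25.6%.

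**3. Sensitivity to what counts as motor.** A few items outside those two domains have a motor element (questionnaire in Appendix IV(a)). I take the items to follow the order of the listed domains, which fits the maxima at 4 points per item.

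| Counted as motor | Points | Share of 156 |
|---|---|---|
| Mobility + ADL | 64 | 41.0% |
| + speech (item 34) and muscle cramps or spasms (item 37), 2 × 4 = 8 | 72 | 46.2% |
| + all of communication (12) instead | 76 | 48.7% |
| + all of communication and all of bodily discomfort (24) | 88 | 56.4% |

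The share passes one half only in the last row. That row counts feeling ignored by people (item 36) and feeling uncomfortably hot or cold (item 39) as motor items.

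**4. What this means for the total score.** The 92 points outside mobility and ADL correspond to 92/4 = 23 items. A one-category improvement on each would lower the total by 23 points with every mobility and ADL item unchanged. This illustrates what the score allows; it does not predict what will happen.

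**5. Set the statements side by side.** Section 4.5 assigns quality of life to PDQ-39 and motor function to UPDRS Part III. Chapters 2 and 3, section 4.3 and the follow-up text assign motor function to both. No passage limits the motor use of PDQ-39 to its mobility and ADL domains. The two sets of statements do not agree.

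**The case against.** **The total may not be what is analysed.** Section 4.5 lists the eight domains with their maxima and does not say whether the total or the domains will be tested. A domain-level analysis is possible under the text. This stands: the 41% and 59% apply to the total. It does not remove the mismatch, because the objective and hypothesis name PDQ-39 without restriction.

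**Share of maximum points is not share of expected change.** This also stands. The percentages describe what the score is made of and do not forecast the result.

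**The choice and combination of secondary scales belong in an analysis plan.** Rules for combining scales and for multiplicity often do, and their absence here is not the point. Which construct an instrument measures is fixed in the protocol's own objective and hypothesis; an analysis plan would carry that out, not redefine it.

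**Three stronger readings are tempting, and the document does not support them.**

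- *Either scale alone would confirm hypothesis 2.* A reader might infer this from the slash in Chapter 3. The objective, the flow chart and the follow-up text join the scales with *and*, and a slash can be shorthand for the same. No either/or success rule is stated.
- *The false-positive risk is therefore inflated.* Two independent tests at 5% would give 1 − 0.95² = 9.75%. This needs the unstated either/or rule. It also counts worsening as success unless the tests are one-sided: with two-sided 5% tests, the chance of a false finding of improvement is 1 − 0.975² = 4.94%. Independence is not the worst case either, since the upper bound for two 5% tests is 10%. Above all, it measures a different error: a rejection when neither scale changes. The issue here is a real non-motor change given the wrong label.
- *PDQ-39 is easier to shift by expectation because patients know they were treated.* The protocol describes no blinded rater for UPDRS-III, so expectation could affect that scale too. The investigator also guides patients through the questionnaires. The text does not allow the two scales to be ranked on this.

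**Conclusion.** The point holds as a mismatch between instrument and claim. Four places use PDQ-39 as a measure of motor improvement or motor disability, while section 4.5 describes it as a quality-of-life scale and reserves the motor examination for UPDRS Part III. On the protocol's figures, 64 of 156 points (41%) of the PDQ-39 total come from mobility and ADL. More generous classifications raise this to between 46% and 56%.

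The consequence depends on the total being used, which the protocol leaves open. If it is, a change confined to non-motor domains could be reported as motor improvement. In either case the trial lacks a quality-of-life objective for a scale it collects at both assessments.

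The scope is one secondary objective and its hypothesis. The primary endpoints (L-dopa onset time and on-time duration) and the sample size do not depend on it. The change is worth making because it alters what the trial may conclude and costs almost nothing.

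**What to change.** Amend the four places together so that they agree with section 4.5.

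1. **Chapter 2 (secondary objective) and Chapter 3 (hypothesis 2):** rest motor improvement and motor disability on UPDRS-III. Add a separate secondary objective and hypothesis for quality of life, measured by PDQ-39.
2. **Section 4.3 (flow chart) and section 4.5 (Follow up visit):** list UPDRS-III as the motor assessment and PDQ-39 as the quality-of-life assessment.
3. **If a patient-reported motor measure is wanted:** name the PDQ-39 mobility and ADL dimensions explicitly and label them as such, apart from the total.

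The cost is wording. The same questionnaires are completed at the same visits by the same patients. The one thing given up is that the PDQ-39 total can no longer be cited in support of the motor claim.
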